## Abstract

**Objectives:**

1) To compare the average cost of an emergency department (ED) visit for various minor musculoskeletal disorders between two models of care (physiotherapist and ED physician or ED physician alone); 2) To evaluate the incremental cost-effectiveness ratio (ICER) of these two models of care over a 3-month period post-initial visit; and 3) To estimate the ICER of three ED models of care (physiotherapist and ED physician, ED physician alone, physiotherapist alone) over a two-year period.

**Methods:**

Obj.1: The costs incurred by participants in the two groups during their ED visit will be calculated using the Time-Driven Activity-Based Costing (TDABC) method. These costs will be compared using generalized linear models. Obj. 2: The ICER of the two models will be evaluated over three months via a cost-utility analysis that will combine costs and effectiveness data (quality-adjusted life years) using both Health system and Societal perspectives (patient + health system costs). Obj. 3: The 2-year ICER of the three above-mentioned models will be estimated using a mathematical model including a decision tree (0–3 months post-visit) and a Markov model (3–24 months post-visit), also using both Health system and Societal perspectives. Data to answer the three objectives will come from data collected during a randomized clinical trial (n = 78, CHU de Québec)which will be supplemented with data obtained via some of the CHU de Québec administrative databases (nominative data; SIURGE (ED management software), Cristal-Net (patient electronic record), and the ED’s pharmacy transactions directory; administrative data: drug costs repository), the literature, and public cost repositories.

**Conclusion:**

This study will help to determine which model of care is most efficient for the management of individuals who come to the ED with minor musculoskeletal disorders. The increased involvement of various health professionals in the management of patients in the ED paves the way for the development of new avenues of practice and more efficient organization of services.

## Introduction

The emergency department (ED) serves as the main gateway and the preferred resource when primary care services are not available, for example in cases of lack of affiliation with a primary care source or inability to see a physician within a reasonable time frame [1–5]. Although pain conditions for which patients decide to go to the ED are varied, they are oftentimes related to a musculoskeletal disorder (MSKD) [6–8].

According to the World Health Organization, MSKDs are characterized by "pain (often persistent) and limitations in mobility, dexterity and general functioning" [9]. MSKDs can affect joints, bones, muscles, spine and multiple regions of the body [9, 10]. The prevalence of these disorders is reported to be significantly higher in women, older people and people with low socio-economic status [11–15]. When they do not receive timely and appropriate care, people with MSKDs tend to make greater use of health care services and resources [16–22]. MSKDs account for up to 12.6% of a country’s total health care costs each year [15] and this figure is expected to rise with the increase in obesity, physical inactivity and the aging of the population [11, 23]. It is therefore essential to study the costs and clinical effectiveness of interventions aimed at managing MSKDs in order to choose the most efficient ones, including in the ED.

Various models of care have been implemented in the ED and studied in recent years to optimize the management of people presenting with MSKDs. These models of care aim to optimize the flow of patients to and in the ED in three distinct phases: "input" (i.e., flow of patients deciding to come to the ED), "throughput" (i.e., flow of patients while in the ED), and "output" (i.e., flow of patients upon discharge from the ED) [24]. Such models of care include for instance fast-track corridors for patients with minor injuries or rapid assessment teams [25]. Some models include the addition of ED nurse practitioners and a variety of health professionals with a usual or extended scope of practice, such as the primary contact physiotherapist or advanced practice physiotherapist [25].

The addition of primary contact physiotherapists in the ED is an emerging model of care that aims to optimize patient flow while in the ED [25]. Several studies conducted in recent years have shown that this model of care is associated with reduced time waited before receiving care, and reduced length of stay in the ED, as well as fewer unnecessary consultations with various health professionals, and less prescriptions of imaging tests and medication, including opioids, and over-the-counter medication [8, 26–29]. In addition, this model of care was associated with fewer repeat visits to the ED for a similar condition for up to one month after the initial ED visit [29]. Thus, management by a primary contact physiotherapist appears to be associated with decreased service and resource use, both at the ED and up to several weeks later. However, very few studies having investigated primary contact physiotherapist care in the ED have looked at its cost-effectiveness.

Indeed, despite evidence of clinical benefits associated with the presence of a primary contact physiotherapist in the ED (effectiveness), scientific evidence remains rather scarce regarding the cost-effectiveness of this model of care. Two studies conducted in primary care settings (primary care clinic and private clinic) report that primary contact physiotherapist management is associated with a slight increase in health-related quality of life and a decrease in total costs compared to usual management by a family physician [30, 31]. In addition, early physiotherapy management was associated with a decrease in total MSKD-related costs for up to two years after initial management [17, 19, 32]. Two cost-minimization studies conducted in Great Britain looked specifically at the costs associated with the integration of a primary contact physiotherapist in the ED compared to usual management by an emergency physician. According to the study by Richardson et al. (2005, n = 766 patients with non-fracture MSKDs), the presence of a primary contact physiotherapist in the ED results in costs equivalent to usual management (emergency physician) [33]. Similarly, according to McClellan et al. (2013, n = 372 patients >16 years of age with a peripheral MSKD), management by a primary contact physiotherapist results in costs at least as high as usual management (emergency physician) [34]. Nevertheless, in addition to having been conducted exclusively in Great Britain several years ago, these two studies only measured the costs of the two models of care compared and not their effectiveness, the authors assuming that the two models compared were equivalent in terms of clinical effectiveness. These studies are thus not considered to be formal economic evaluation according to current guidelines, but rather a costing exercise, in that a cost-effectiveness analysis accounts for the uncertainty associated with the effects of the interventions being compared [35]. To our knowledge, no other study has examined the cost-effectiveness of primary contact physiotherapy in the ED. Furthermore, no study has assessed whether involving primary contact physiotherapists in the ED have a long-term impact on use of health system services and resources for persons with minor MSKDs. Consequently, further evidence is needed on the efficiency of integrating a primary contact physiotherapist in the ED compared to usual management by an emergency physician.

Therefore, the general objective of this project is to evaluate the efficiency of different models of care for the management of minor MSKDs in the ED. More specifically, the objectives are to:

Compare the average costs of an ED consultation and care for various MSKDs, according to two models of care:
Usual management by an emergency physicianPrimary contact physiotherapist management + emergency physician managementEvaluate the incremental cost-effectiveness ratio (ICER), from both Health system and Societal perspectives, of these two ED models of care for the management of MSKDs over a three-month period post-initial ED visit.Estimate the ICER between three ED models of care for MSKD management over a two-year period from both Health system and Societal perspectives:
Usual management by an emergency physicianPrimary contact physiotherapist management + emergency physician managementPrimary contact physiotherapist management alone

## Materials and methods

### Study design and costing approaches

This study is composed of three distinct designs, one per objective. The costing approach used for Objective 1 will be Time-Driven Activity-Based Costing (TDABC), which involves determining the per-minute costs associated with each care process included in a care pathway by multiplying the cost per minute of each care process by its duration. Details on this costing approach and its application to the ED have been described by one of the authors elsewhere [36]. Objective 2 will be achieved through a cost-utility analysis approach in which health care costs at the ED visit and those reported at the 1- and 3-month follow-ups will be compiled and combined with the utility scores obtained at the same measurement times, from both Health system and Societal perspectives. Cost-utility analysis is favored in Canada since it uses a generic outcome measure allowing comparison of the health gains associated with several different interventions, such as different models of care [35].

The ICER between the three ED models of care for the management of MSKDs over a two-year period (Objective 3) will be estimated using a cost-effectiveness analysis via a hybrid mathematical model. This model will consist of a decision tree covering the period from the initial ED visit up to three months post-initial visit, and a Markov model starting three months post-initial ED visit and ending 24 months (two years) after the ED visit. The decision tree provides a simple and clear illustration of a patient’s possible short-term care pathways following a new intervention [35, 37]. In addition to reporting the different interventions used, the decision tree also allows for the inclusion of adverse events following the initial intervention, such as a new ED visit for the same condition, and for repeating an intervention over time as needed (e.g., new visit in the ED a few days after the initial visit and then a new visit two months later for the same condition) [35, 37]. It also permits to determine the proportion of disability associated with each of the three ED models of care.

Several considerations guided the choice of the time horizon for the Markov model. First of all, to be considered chronic, a musculoskeletal disorder must be present for at least three months [38]. Moreover, approximately 30% of people presenting with MSKDs report pain and functional disability lasting more than 12 months after the onset of their condition. Furthermore, studies on MSKD care in primary care or the ED have had follow-up periods ranging from six to 24 months (e.g. [26, 39–42]). Thus, the Markov model will cover a 24-month period. It will include two-week cycles in order to capture the clinical evolution of the patients included.

### Population of interest

Inclusion and exclusion criteria for the population of interest are described in Box 1. The population targeted covers persons with a peripheral or spinal MSKD, a P3, P4 or P5 triage category at the ED (Canadian Triage and Acuity Scale [43]), and that are aged between 18 and 80. Having a major MSKD, red flag or associated unstable condition are criteria for exclusion.

**Box 1 pone.0277369.g001:**
[figure not shown]
Inclusion and exclusion criteria for the population of interest.

### Data collection

Objectives 1, 2 and 3 will be achieved in part using data collected through a two-arm pilot pragmatic randomized clinical trial (RCT) conducted in the ED of the CHUL, one of the five sites of the CHU de Québec—Université Laval (UL) (Quebec City, Canada) from September 2018 to March 2019 (n = 78). This trial aimed to compare the effects of management by a primary contact physiotherapist to usual care provided by an emergency physician for persons presenting with a minor MSKD on their clinical course (pain and pain interference) and the use of resources at ED discharge and after 1 and 3 months post-visit [29]. Two groups of participants were compared: one group managed by a primary contact physiotherapist and an emergency physician and one group managed by an emergency physician alone.

Data were collected at the initial ED visit and at the one- and three-month post-visit follow-ups. While more details of the data collection procedures can be found in our previous paper [29], any person presenting to the ED who met the inclusion and exclusion criteria was seen by a member of the research team who confirmed eligibility, obtained informed consent, and ensured completion of baseline questionnaires. The participant was then randomized to either study group: primary contact physiotherapist + emergency physician management or usual management by the emergency physician alone. After the ED visit was completed, participants were contacted at 1 and 3 months either by phone or email to complete post-visit follow-ups. The supplementary data needed to meet the three Objectives will come from some of the CHU de Québec—UL administrative databases (nominative data: SIURGE (ED management software), Cristal-Net (patient electronic record), and the CHUL’s ED pharmacy transactions directory; administrative data: prescription and over-the-counter drug costs repository), the scientific literature, and public cost repositories (e.g., salaries of general practitioners and specialists, see https://www.msss.gouv.qc.ca/inc/documents/ministere/acces_info/seance-publique/etude-credits-2018-2019/Reponses-aux-questions-generales-et-particulieres-RAMQ.pdf; laboratory analysis costs, see https://publications.msss.gouv.qc.ca/msss/fichiers/2017/17-922-05W.pdf).

Of note, the study population for the model of care consisting of primary contact physiotherapist management and discharge from the ED was not observed at all during the pilot pragmatic RCT. Consequently, this model of care will have to be modeled, and therefore cannot be studied in the context of Objectives 1 and 2, which are based on RCT data. All the parameters needed to represent this care model within Objective 3 (probabilities, costs, measures of effectiveness) will be taken from a literature review, an approach regularly used in economic evaluation [44]. However, the studies from which the metrics will be derived will need to have a sample that meets the same inclusion criteria as those presented in Box 1. Data extracted from the literature will be validated with members of the research team and with experts in the field of emergency medicine, MSKDs and rehabilitation if necessary during the construction of the hybrid model [35].

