**Fig 1 pone.0277369.g002:**
[figure not shown]
Mapping of a hypothetical care pathway in the ED using the Time-Driven Activity-Based Costing.

The decision tree (Objective 3) will be created to reflect the results of the RCT as closely as possible and will therefore include all possible interventions and services used by a participant following the initial visit to the ED for each model of care considered (Fig 2). The pruning of each terminal node containing less than 5% of the participants will be determined based on discussions with a panel of experts. The conditional probability of ending up in each of the remaining terminal nodes of the decision tree will be used to calculate the proportion of disability associated with each care model (Fig 2). The disability proportions obtained for each model of care will be used to determine the number of individuals in each state at entry in the Markov model (Fig 3). The Markov model will then be used to calculate the long-term costs and effectiveness over 2 years of each of the model of care based on the level of disability estimated in the decision tree [35, 37].

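### The third model of care has no place for eligible patients passed to the physician during the visit, and its source rule would admit literature that leaves them out

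*Protocol article*

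**What the plan says.** The objectives at the end of the Introduction list three models for the two-year comparison: emergency physician, physiotherapist plus emergency physician, and physiotherapist alone.

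For the first two, the Data collection section describes entry at presentation: "any person presenting to the ED who met the inclusion and exclusion criteria was seen by a member of the research team". Allocation follows eligibility, consent and baseline questionnaires: "The participant was then randomized to either study group: primary contact physiotherapist + emergency physician management or usual management by the emergency physician alone". The Population of interest section sets the target: "The population targeted covers persons with a peripheral or spinal MSKD, a P3, P4 or P5 triage category at the ED", with an age range and exclusions for major disorders, red flags and unstable conditions.

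For the third, Data collection says that "the study population for the model of care consisting of primary contact physiotherapist management and discharge from the ED was not observed at all" in the pilot trial. Its probabilities, costs and effectiveness values are all to come from literature. Source studies "will need to have a sample that meets the same inclusion criteria as those presented in Box 1", and extracted data are to be validated with the team and, if necessary, with experts.

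The decision tree, described under Data analysis and interpretation of results, is to mirror the trial's results as closely as possible and to "include all possible interventions and services used by a participant following the initial visit to the ED for each model of care considered".

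**The concern.** A comparison of care strategies needs each strategy to be followed in the same people from the same starting point. The two trial arms meet this: a participant stays in the allocated arm however the visit ends. The third model is worded differently. Data collection builds discharge after physiotherapist management into its description, and discharge happens after entry. The label in the objectives does not help. A patient who starts with the physiotherapist and then sees the physician is no longer managed by the physiotherapist alone, and on the wording looks like a case of the combined model.

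Handed-over patients therefore have no stated place in the third model. Since every parameter of that model comes from literature, its definition decides which studies qualify. If the chosen studies report only patients whom the physiotherapist discharged, the third model loses its costlier and possibly less well patients while the other two keep theirs. The project is meant to show which model is most efficient, so the third could be favoured partly because of who was counted.

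**Working it through.** **1. The definitions side by side.**

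| Model | Who is in it | When membership is fixed |
|---|---|---|
| Physician alone | Eligible, consenting, randomised | Before care |
| Physiotherapist + physician | Eligible, consenting, randomised | Before care |
| Physiotherapist alone | Managed by the physiotherapist (objectives), and discharged (Data collection) | Not stated; on the wording, possibly at the end of the visit |

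**2. Do the safeguards in the text close the gap?**
- *Box 1 match.* It concerns criteria at entry. A study that enrolled Box 1 patients but reports only those discharged by the physiotherapist passes.
- *Scope of the tree.* The sentence on interventions and services covers what follows the initial visit. A handover happens during it. The tree is also modelled on a trial in which this pathway did not occur.
- *Sensitivity scenarios.* The three listed deal with missing utility scores, outliers and the definition of the Markov states. None varies a handover share.
- *Validation by team and experts.* No criterion on this point is given.

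**3. Possible size.** The document gives no cost, saving or handover share for the third model, so there is no figure to reproduce. All inputs below are assumptions.

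*Against the combined model.* Let C be the physician component of the visit cost and h the share of eligible patients handed over, each taken to cost the same as under combined care. Counting completers only credits a saving of C per patient. Counting everyone who starts gives (1 − h)C. The relative overstatement is C/[(1 − h)C] − 1 = 1/(1 − h) − 1.
- h = 0: 0
- h = 0.10: 1/0.90 − 1 = 0.111, or 11%
- h = 0.20: 1/0.80 − 1 = 0.250, or 25%
- h = 0.30: 1/0.70 − 1 = 0.429, or 43%

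*Against the physician alone.* Set the physician-alone visit cost to 1. Let a be the cost of a patient discharged by the physiotherapist and b that of a patient handed over. The mean over all starters is (1 − h)a + hb, so counting completers only overstates the saving by h(b − a). With a = 0.8 and b = 1.2 the apparent saving is 1 − 0.8 = 0.20. Over all starters:
- h = 0.10: 1 − (0.72 + 0.12) = 0.16
- h = 0.20: 1 − (0.64 + 0.24) = 0.12
- h = 0.30: 1 − (0.56 + 0.36) = 0.08

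Over a from 0.7 to 0.9, b from 1.0 to 1.5 and h from 0 to 0.30, the overstatement runs from 0 to 0.30 × (1.5 − 0.7) = 0.24. It is zero if h = 0 or b = a. At the unfavourable corner a = 0.9, b = 1.5, h = 0.30, an apparent saving of 0.10 becomes 1 − (0.63 + 0.45) = −0.08, so the sign changes.

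These figures cover the cost of the ED visit only. They do not measure the effect on QALYs or on the two-year ICER.

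**The case against.** A reader might go further and infer that the third model is by definition a selected group of successes, so that its saving is overstated. The document does not support that, for these reasons.

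- The sentence in Data collection can be read as listing the steps of care (the physiotherapist manages, the patient leaves) and not as picking patients by outcome. The Abstract and the objectives name the model without mentioning discharge.
- The same paragraph requires source samples to meet Box 1, which aims at the same population at entry.
- The decision-tree figure is not reproduced in the text at hand and may hold a referral branch. Probabilities are among the parameters to be taken from literature, so a single certain route is not assumed.
- No source has been chosen and no saving is stated. Nothing shows that h exceeds zero in this population.
- Patients with a red flag or major disorder do not make the case. They are excluded at entry from all three models, unless missed at screening.
- The authors say openly that this model was not observed, and the Discussion names the difficulty of finding literature data for Objective 3 as a limitation.

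All of this stands against the stronger claim. It does not settle the narrower one. On either reading of the sentence, the text does not say how a handed-over patient is counted, and the Box 1 rule does not screen out completers-only studies. An article may leave detailed branching rules to a fuller document. The definition of a comparator and the rule for admitting its data, however, are both stated here, and as stated they leave this gap.

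**Conclusion.** The point holds as a weakness in how the third model and its source rule are worded. The two trial arms keep everyone randomised, whereas the third model has no stated place for eligible patients passed to the physician during the visit. The source rule would accept studies that omit them. The result could be a third model that looks cheaper and more effective than it is.

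The bias is a possibility and is not shown to exist. It arises only if the sources used are restricted to patients discharged by the physiotherapist, some eligible patients are handed over, and those patients cost more or fare worse. The percentages in the working are conditional on assumed handover shares and on handed-over patients costing the same as combined care. The direction for QALYs is plausible but unquantified.

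**What to change.** 1. In the objectives and in Data collection, define the third model for Objective 3 as a strategy applied to all Box 1-eligible patients at entry, starting with the physiotherapist alone. State that patients passed to the physician stay in this model, with both professionals' costs and their own QALYs.
2. Add to the source rule that values must be reported for all patients who start with the physiotherapist.
3. Where a source reports completers only, include a handover branch in the decision tree and vary its probability in the probabilistic sensitivity analysis.

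This concerns who is counted in the analysis and sets no rule on when a patient should be handed over. The cost is some rewording and one extra branch with an uncertain probability. No new participant data are needed. Fewer studies may qualify directly, and the third model's ICER may come out less favourable.

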As part of the cost-utility analysis (Objective 2) and hybrid mathematical model (Objective 3), the efficiency of the ED models of care will be assessed using an incremental cost-effectiveness ratio (ICER). The resulting ICER will be reported in terms of incremental cost per quality-adjusted life years (QALY) gained, between the models of care. The follow-up costs of each participant recorded via the self-administered follow-up questionnaires completed at 1 and 3 months during the pilot pragmatic RCT will be added to the distribution of ED visit costs for each individual obtained under Objective 1. Once all costs have been added, an average will be calculated to obtain an average cost per participant at 3 months, for each model of care (Objective 2 & 3 –decision tree). The questionnaires provided data on resources used by each participant during follow-up such as ED re-visits for the same condition, number of consultations with other health professionals in the public and private sector, imaging tests used, etc. The costs of all resources used in the public healthcare system will be drawn from public cost repositories data from the *Régie de l’assurance-maladie du Québec* (RAMQ) (costs related to the emergency physician and other physicians consulted, drugs, laboratory analysis, imaging tests) [47]. Hourly rates for the primary contact physiotherapist and other health professionals consulted (e.g., massage therapist, chiropractor, osteopath) will be derived from a search of the grey literature and will be based on rates in effect within the private healthcare system, since the majority of these professionals work within this system [47]. Costs related to the use of technical aids (e.g., cane, crutches, walker) will also come from a grey literature search. It should be noted that the salary data available from human resources for all healthcare professionals (physicians and allied health professionals) considered will not allow for variability in hourly costs. The only source of variability considered for the purpose of these analyses will be that related to the time required for ED processes. Utility scores were obtained at the initial visit [48] and at 1 and 3 months using the EQ-5D-5L, a generic standardized questionnaire designed to measure health status in an economic and clinical evaluation [49]. The EQ-5D-5L has been found to be reliable, valid, and sensitive to change [50, 51]. The difference in utility scores between the 3-month follow-up and baseline will be calculated for each participant using area-under-the-curve analyses. Once the difference in utility scores will be calculated for each participant, the differences will be averaged to obtain the average gain or loss in utility scores per ED care model. The mean gain or loss in utility scores will then be transformed into QALYs. The efficiency values and the costs from 3 to 24 months required to run the Markov model (Objective 3) for the three models of care will be taken from the literature.

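### In the 0–3 month part of Objective 3, the physiotherapist-alone model is built wholly from outside studies and set against trial data with no stated common comparator.

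*Protocol article*

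**What the plan says.** The Data collection section states that the physiotherapist-alone model "was not observed at all during the pilot pragmatic RCT" and must therefore be modelled. Its sourcing rule is comprehensive: "All the parameters needed to represent this care model within Objective 3 (probabilities, costs, measures of effectiveness) will be taken from a literature review". Two safeguards follow. Source samples must satisfy the Box 1 inclusion criteria, and extracted data are validated by the research team and, if necessary, by experts.

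The two observed models are sourced differently for months 0–3. Under Data analysis and interpretation of results, "The decision tree (Objective 3) will be created to reflect the results of the RCT as closely as possible". Under Study outcomes, ED visit costs and questionnaire-based follow-up costs from the trial are combined into "an average cost per participant at 3 months, for each model of care", and utility enters as each participant's change from baseline on the EQ-5D-5L.

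The two parts of the model are linked. The disability proportions from the tree "will be used to determine the number of individuals in each state at entry in the Markov model". For months 3–24, effectiveness and costs "for the three models of care will be taken from the literature".

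**The concern.** Objective 3 promises ratios between all three models. Physician alone and physiotherapist plus physician are compared within one randomised trial, in one hospital and with one set of unit costs. The third model enters from other studies. If its values are placed beside the trial's with nothing in common to calibrate them, any difference between the source studies and the Quebec trial is read as an effect of removing the physician.

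Cost shows this most plainly. The trial arms are costed from the hospital's own finance data and time estimates, from public Quebec repositories and from local private rates. The third model's costs would come from publications. The Introduction itself discounts the two earlier ED costing studies as British and several years old.

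At stake is where the only unobserved model ranks. The Discussion says the project will help identify the most efficient model.

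**Working it through.** The article gives no sample size, precision or effect figure for Objective 3, so there is no stated number to reproduce. The check has three steps.

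**1. Sources side by side**

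| Input | Two observed models | Physiotherapist alone |
|---|---|---|
| Tree probabilities, 0–3 months | Trial results | Literature |
| Costs, 0–3 months | Trial resource use and local unit costs | Literature |
| Utility, 0–3 months | Trial EQ-5D-5L change, Canadian value set | Literature |
| Markov starting states | Trial-based tree | Literature-based tree |
| Costs and effectiveness, 3–24 months | Literature | Literature |

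The mismatch arises directly in 3 of 24 months. The remaining 21 months (21/24 = 87.5%) use literature for all models, but the starting states carry the earlier difference forward.

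**2. Do the planned safeguards remove it?**

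- Box 1 criteria and validation narrow case-mix differences. They do not equalise country, period, usual care, unit costs, outcome recording or prognosis within the criteria.
- The Monte Carlo analysis, as described, covers uncertainty in the parameters. It does not cover a systematic offset between sources.
- The three scenarios concern extreme utilities for missing data, exclusion of outliers, and Markov states defined by pain interference. None varies where the third model's values come from.
- The limitations in the Discussion mention that medium- and long-term data may be hard to find, but not this bias.

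**3. What an offset does**

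Let g be the mean utility gain from baseline in the trial's physician-alone arm, d the true difference for physiotherapist alone, and b the amount by which gains in the source study differ from the trial in all its arms.

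- Unanchored: (g + b + d) − g = d + b.
- Anchored on the source study's own physician arm: (g + b + d) − (g + b) = d.

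With assumed d = 0.03 and b = 0.05, the first gives 0.08 and the second 0.03.

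Here b must be an offset in gain. If a source study has utilities higher by a constant a at both times, then (u3 + a) − (u0 + a) = u3 − u0, and the offset cancels in the change-from-baseline measure.

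Illustrative size, with assumed offsets and no true difference between models:

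- QALY offset over 3 months = b × 0.25, with b taken as averaged over the period. For b = 0.01, 0.02 and 0.05 this is 0.0025, 0.005 and 0.0125.
- Spurious ratio = cost offset / QALY offset. The lowest is 50 / 0.0125 = 4,000 dollars per QALY. The highest is 200 / 0.0025 = 80,000 dollars per QALY.

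These figures show sensitivity only. The document supports no particular offset.

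**The case against.** The strongest reply is that the article never says single-arm values will be used. It names probabilities, costs and effectiveness measures from a literature review and does not say how they will be combined with the trial arms. A fuller plan might specify contrasts. This stands in part: the unanchored reading is an inference. It is the natural one, however. If a contrast were applied to the trial's physician-alone arm, the baseline would come from the trial, and not all parameters would come from the literature. The sourcing rule is stated, not merely left out.

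It is also fair that the model is openly declared as unobserved, that Box 1 and validation reduce case-mix differences, and that literature serves all three models after month 3. These points limit the scope of the problem but do not remove it.

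Four stronger readings are tempting, and the document does not support them:

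- *The whole of Objective 3 is compromised.* The contrast between the two observed models stays randomised for months 0–3, and Objectives 1 and 2 are untouched.
- *Ready anchors already exist.* The two British studies (n = 766 and n = 372) examined "integration of a primary contact physiotherapist in the ED compared to usual management by an emergency physician", but the Introduction says they measured costs and not effectiveness, so they cannot anchor effectiveness. The other ED results it cites are mainly process outcomes, and the repeat-visit result is from this trial itself. Whether suitable contrasts exist must be established by the review.
- *The third model will look falsely precise because published samples are larger.* The article does not say which studies or Monte Carlo distributions will be used, so no precision ratio can be given.
- *Any difference in utility level between studies becomes a QALY difference.* A constant level difference cancels, as shown above.

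**Conclusion.** The concern holds for the physiotherapist-alone model in the 0–3 month decision tree and for what that tree passes to the Markov model. Followed as written, the sourcing rule compares outside studies with trial arms without a common comparator, and no planned safeguard or scenario addresses the resulting bias.

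Its size and direction are unknown from the document. The 4,000–80,000 dollars per QALY range is an illustration under assumed offsets, not an estimate. The conclusion rests on reading the statement that all parameters come from the literature at face value. It deserves correction before the literature extraction begins, because it bears on where one of the three models ranks.

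**What to change.** Amend the sourcing rule in Data collection, with a matching sentence under Data analysis:

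- **Probabilities and effectiveness.** Where comparative studies exist, extract the within-study contrast of physiotherapist-alone versus emergency physician care (risk ratio, odds ratio or mean difference; for utility, the difference in change from baseline). Apply it to the trial's physician-alone arm. The third model is then compared with physiotherapist plus physician through the same comparator.
- **Uncertainty.** Draw both the trial baseline and the contrast in the Monte Carlo analysis, so that the third model carries both.
- **Costs.** Take resource use, not published costs, from the literature and price it with the same Quebec unit costs as the trial arms.
- **Fallback.** Where only single-arm values exist, label the third-model comparison unanchored and exploratory, and add a scenario that varies the between-study offset over a stated range.

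Anchoring assumes that the contrast carries over to the Quebec setting on the chosen scale. That assumption should be stated.

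The cost is a change of wording and somewhat more extraction work, with no new patient data. Uncertainty around the third model will be wider.
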